### Sample size

We aim at an overall power of 0.8 (alpha 0.05) to detect a difference of at least 0,5 SD in the Patient Activation Measure. We consider 0,5 SD to be a clinical relevant difference based on the article of Norman et al. [25]. To be able to detect such a difference we need 63 individuals in each arm in a non-clustered study. We used a multiplication factor of (1 + (k-1)*ICC), with k indicating the average cluster size, which is 12, and ICC indicating the intraclass correlation, which is the fraction of total variation in the data that is accounted for by between-group variation. For an ICC of 0.05 this amounts to a multiplication factor of 1.55, and thus 98 (1.55*63) individuals in both the intervention and the control arm.

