### Study population

The study population consists of older people living at home and receiving home care or residing in one of 16 participating care homes of Laurens, a care organisation in Rotterdam, the Netherlands. Residents of care homes generally suffer from one or more chronic conditions and 32 % are totally dependent on others for daily care needs [13]. Their average life expectancy is 3,7 years, and their health condition often involves important health care decisions in a relatively short time frame.

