### Assessment and data collection

At baseline, in personal structured interviews, patient activation will be measured (PAM-13) [17]. The PAM assesses patients’ knowledge, skill and confidence in self- management. Also, generic Health-Related Quality of Life as measured by the SF-12 [18] and satisfaction with health care as measured by the PSQ-18-SF6 [19] will be assessed.

At 12 month follow-up participants will be interviewed again and their competence will be assessed with an adapted version of the Mini-Cog [20]. If participants are competent, the questions of the SF-12 [18], PAM [17], and PSQ-18-SF6 [19] will be asked. We will also ask whether participants completed an advance directive and assigned a proxy decision-maker. In the intervention group, open (qualitative) questions will be asked about how the patient experienced the ACP program.

If the Mini-Cog indicates that participants are no longer competent, a proxy, assigned by the patient at the start of the study, will be approached for a telephone interview. This interview will include the PSQ-18-SF6 [19] and a caregiver activation measure (CAM) [21]. Completion of an advance directive and assignment of a proxy decision-maker by the participant will be assessed. In the intervention group, open (qualitative) questions will be asked about how the relative and the patient experienced the ACP program.

If people pass away during the 12 month follow-up, a proxy, assigned by the patient at the start of the study, will be approached for a telephone interview. This interview will address characteristics of the dying process, quality of dying [16], PSQ-18-SF6 [19], feelings of anxiety and depression of the relative as measured by the HADS [22]. In the intervention group, open (qualitative) questions will be asked about how the relative and the patient experienced the ACP program.

In a medical file study, we will investigate whether people have an advance directive in their medical file (and study its content). Moreover, we will study the medical care people receive during 12 months after inclusion, such as hospitalizations (number, length of stay), use of homecare, palliative care, diagnostic procedures and specific treatments (e.g. medication, mechanical ventilation, resuscitation, chemotherapy, artificial fluids or food, surgery or antibiotics).

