### Statistical analysis

Analyses will be performed following the intention-to-treat principle. Descriptive statistics will be used to summarize characteristics of the residents, the care homes and of people receiving home care. Characteristics of participating individuals (age, gender, socio-economic status, educational level) will be compared at baseline between the intervention and control (usual care) group using independent sample t tests and Chi^2^ tests.

Multivariate analysis will be used to compare differences between the intervention group and the control group at baseline and to compare differences in changes after 12 months following the inclusion. Patient characteristics, TFI score, MMSE score and place of residence will be used as covariables. All statistical tests will be considered significant if *p* < 0.05. Missing items will be imputed by the peoples’ own average score if they have completed at least 50 % of the items.

The cost-effectiveness of ACP will be assessed by calculating the incremental cost-effectiveness ratio (ICER), defined as the difference in costs of ACP compared to usual care, divided by the average change in effectiveness, with the patient activation as primary outcome measure [17]. We will perform a sensitivity analysis to assess the stability of the results to changes in costs and effectiveness parameters. Because of the short time horizon, costs and effects will not be discounted.

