#### Limitations

First, selection bias in identifying potential study participants cannot be ruled out. To prevent this as much as possible, we have prepared clear in and exclusion criteria. These criteria are the same in both the intervention arm and the control arm.

Second, follow-up of the respondents is limited to 12 months after inclusion, while the average life expectancy of the study group is 3,7 years [13]. We expect that respondents may need to make important health care decisions within the timeframe of the study, given their frailty, but we may miss important decisions. However, the main goal of the study is to increase patient activation, and such activation is possible without major decisions taking place. Examples of this are conversations with relatives and health care professional about preferences regarding future care.

Third, dropout will be an inevitable limitation of the study. Dropout can occur due to, for example, loss of contact. However, we ask staff members of Laurens to report participants moving house. If people move they can remain included in the study. Dropout can also take place because people are no longer interested in participation. However, we expect that the number of dropouts will be similar in both groups. If participants die during follow-up, one of their relatives will be asked to complete a bereaved carer questionnaire.

Fourth, the extent to which medical files reflect actual care can be questioned. We are not sure that all received treatments will be written down in medical files.

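### The 98 per arm reaches power 0.80 for 0.5 SD only if every participant provides a 12-month PAM, and no step allows for death, loss of competence or dropout

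*Protocol article*

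**What the plan says.** The Sample size section sets the target: "We aim at an overall power of 0.8 (alpha 0.05) to detect a difference of at least 0,5 SD in the Patient Activation Measure". It says that "we need 63 individuals in each arm in a non-clustered study", takes an average cluster size of 12 and an ICC of 0.05, obtains a design effect of 1.55, and concludes "and thus 98 (1.55*63) individuals in both the intervention and the control arm". No further factor is applied and no other target is given.

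Other sections bear on how many of the 98 will contribute the primary outcome:

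- *Assessment and data collection* restricts the 12-month PAM to participants found competent. "If the Mini-Cog indicates that participants are no longer competent, a proxy, assigned by the patient at the start of the study", is interviewed instead, with a caregiver activation measure and the satisfaction questionnaire but not the PAM. The proxy of a participant who has died is given no activation measure.
- *Study population* says of care home residents: "Their average life expectancy is 3,7 years". *Limitations* applies the same figure to the study group, beside a follow-up of 12 months.
- *Limitations* also says that "dropout will be an inevitable limitation of the study". It expects similar numbers in both groups and gives no rate.

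*Study design* makes neighbourhoods the clusters, randomised in pairs matched on income. Their number is not stated.

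**The concern.** The calculation counts each of the 98 as a completed primary outcome. The article's own assessment schedule and population make that implausible: participants are at least 75, frail, and may enter with an MMSE score as low as 17. Those who die, lose competence or withdraw have no 12-month PAM. An expectation of equal dropout in both arms speaks to bias and does not restore lost precision.

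At stake is the power quoted for the primary comparison. If 98 is the number enrolled, the trial has less than its stated 0.8 for the difference that it calls clinically relevant, unless something not credited in the calculation makes up the shortfall. A reader who weighs a null result against the planned power would then be using too favourable a figure.

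**Working it through.** **Inputs from the article.** Difference 0.5 SD; alpha 0.05 (taken as two-sided, which reproduces the 63); power 0.80; cluster size k = 12; ICC = 0.05; 98 per arm, 196 in total. The loss rate L is not given and is varied as an assumption.

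**1. Reproduce the stated figure.**

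- Unclustered n = 2 × (1.96 + 0.8416)² / 0.5² = 62.8, so 63 per arm.
- Design effect = 1 + (12 − 1) × 0.05 = 1.55.
- 63 × 1.55 = 97.65, so 98 per arm.
- SE = √(2 × 1.55 / 98) = 0.1779 SD; 0.5 / 0.1779 = 2.811; power = Φ(2.811 − 1.960) = 0.803.

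The 98 is therefore correct for 98 analysed. The product 1.55 × 63 accounts for the whole figure and leaves no room for an unreported attrition factor.

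**2. Power when a fraction L has no 12-month PAM.** Take n = 98(1 − L) and analysed cluster size k = 12(1 − L), so that DE = 1 + (k − 1) × 0.05 falls as clusters shrink. SE = √(2·DE/n). Power with a normal reference is Φ(0.5/SE − 1.96).

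| Loss (assumed) | n per arm | k | DE | Power, normal | Power, t with 14 df |
|---|---|---|---|---|---|
| 0% | 98 | 12 | 1.55 | 0.803 | 0.744 |
| 10% | 88.2 | 10.8 | 1.49 | 0.776 | 0.716 |
| 20% | 78.4 | 9.6 | 1.43 | 0.745 | 0.683 |
| 25% | 73.5 | 9.0 | 1.40 | 0.726 | 0.664 |
| 35% | 63.7 | 7.8 | 1.34 | 0.684 | 0.621 |

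With a normal reference, power drops below 0.80 between 1% and 2% loss (0.800 at 1%, 0.798 at 2%). Letting the design effect shrink is the kinder choice: holding k at 12 gives 0.682 at 25% loss.

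**3. How large might the loss be?** If the 3.7 years is read as a mean survival with constant hazard, deaths in 12 months are 1 − exp(−1/3.7) = 0.237. If the hazard rises with time at the same mean, first-year deaths are lower: 16% for a Weibull shape of 1.25 and 11% for 1.5 (shapes assumed). These cover death only; loss of competence and withdrawal add to them.

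**4. Number of clusters.** 196/12 = 16.3, or 98/12 = 8.2 per arm. This is derived, and it is not the 16 participating care homes, which are not the clusters. With 8 neighbourhoods per arm, an unpaired cluster-level comparison has 2 × 8 − 2 = 14 df. The last column of the table uses the noncentral t distribution on 14 df.

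**5. Detectable difference at 25% loss, 80% power.** SE = √(2 × 1.40 / 73.5) = 0.1952. Normal reference: 2.8016 × 0.1952 = 0.55 SD. With 14 df: 0.59 SD.

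**6. Possible gain from baseline PAM.** Adjustment at correlation r multiplies the SE by √(1 − r²). At an assumed r of 0.5 and 25% loss, SE = 0.1952 × 0.866 = 0.1690. Power is then 0.84 (normal) or 0.785 (14 df).

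**The case against.** Five things can be said for the plan.

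*The 98 may be the evaluable number.* The article is condensed and its flow chart is not shown. However, it gives no other target and no inflation step, so nothing in the text supports this reading. If it is what was meant, one sentence settles the attrition point.

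*The loss rate is the reviewer's assumption.* This stands. The 3.7 years is introduced for care home residents in general, participants must be competent at entry, and some live at home. A reader might infer that about a quarter will die within the year; the documents do not establish that. A range is therefore shown, and even 10% loss leaves power at 0.78.

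*Baseline adjustment may recover the power.* This also stands in part. Baseline PAM is measured and the analysis compares changes. But the sample size takes no credit for it, and baseline PAM is not named among the covariables. Simple change scores give no gain at a correlation of 0.5.

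*The 14 df are not in the plan.* Correct: the analysis model is described only as multivariate, and matching on income might reduce between-cluster variation. A paired analysis of about 8 pairs would, however, have fewer df (7). The cluster-count point is secondary and conditional.

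*Nothing is miscalculated.* Also correct. A reader might take this as an arithmetic error, but the multiplication is right; the fault is an unstated assumption of complete follow-up. Likewise, a null result should be judged mainly by its confidence interval, which limits the harm from a wrong planned power.

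**Conclusion.** The point holds. On the article's own inputs, 98 enrolled per arm gives power 0.80 for 0.5 SD only with virtually complete 12-month PAM data, and the article describes several routes by which those data will be missing.

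The shortfall from attrition alone is moderate: about 0.78 to 0.68 over an assumed 10% to 35% loss. It rests on a normal reference, ICC 0.05, equal clusters and no baseline adjustment. If an unpaired cluster-level t reference with 14 df is used as well, the figure is about 0.74 with no loss and 0.66 at 25% loss.

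A stronger conclusion, that the trial cannot reach 0.8, does not follow. With baseline-PAM adjustment it might, depending on a correlation and a model that the article does not give. Nor do the documents state that there are 16 clusters; that is an inference from 196/12.

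**What to change.** In the Sample size section:

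- State the assumed proportion without a 12-month PAM (death, loss of competence and withdrawal together) and the number of neighbourhoods per arm.
- Restate the power or detectable difference for 98 enrolled per arm. At an assumed 25% loss this would read: power about 0.73 for 0.5 SD, or 80% power for about 0.55 SD. With a 14-df reference the figures are 0.66 and 0.59 SD.
- If 98 is meant as the number with an evaluable 12-month PAM, say so.
- Alternatively, name baseline PAM as a covariable in the Statistical analysis section and take explicit credit for it with a stated correlation. At 0.5 and 25% loss, power would be about 0.84 (normal) or 0.785 (14 df).

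The cost is one rewritten paragraph and, unless credit for baseline adjustment is taken, a less favourable stated figure. No extra enrolment is required.

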### Study procedures

Staff of the care organisation will use a checklist to assess whether participants - either living in care homes or at home - are potentially eligible for the study (see Fig. 1: CONSORT Flow chart). These people will be informed about the study and will be asked to participate by the research team. Furthermore, in the intervention group they will be invited to visit an informative meeting about the study and the intervention.

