## Methods/Design

### Study design

We will conduct a cluster Randomized Controlled Trial (RCT) among older people living in care homes or at home receiving home care, following the CONSORT guidelines. The clusters will consist of neighbourhoods. In the Netherlands, standardized household incomes have been calculated per neighbourhood. We will order neighbourhoods according to these standardized incomes to control for differences in income per study arm, since income is related to health [12]. Neighbourhoods will be randomized per set of two neighbourhoods with comparable household incomes to either the control or intervention condition.

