### Inclusion criteria

In order to be eligible to participate in this study, an older person must meet all of the following criteria:≥75 years of age;Mentally competent, as measured by judgement of caregiver and a Mini–Mental State Examination (MMSE score > 16 [14];Fluent in Dutch;Being frail, as measured by the Tilburg Frailty Index [15] (TFI score of 5 or more)

These criteria apply for both people living in care homes and people living at home and receiving home care. Older people who move during the follow-up of the study can remain included in the study.

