**Fig. 1 Fig1:**
[figure not shown]
CONSORT flow chart

People who express an interest in the study, will be interviewed face-to-face by one of the researchers (AO, LJ). During this interview, they will receive additional information about the study. When individuals fulfil the inclusion criteria of the study and want to participate, written informed consent will be obtained. Subsequently, the baseline assessment will be completed and the intervention will be carried out in the intervention group. At 12 months after inclusion in the study, participants will be approached again by the researcher to complete a face-to face follow-up assessment. With written permission of the participants, data will be extracted from medical files with the use of a checklist, 12 months post-inclusion.

The independent Ethics committee of Rotterdam (Medisch Ethische Toetsingscommissie) has given approval for the study to be performed.

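### Only the intervention arm is invited to a meeting about the intervention, apparently before consent and baseline PAM-13, so recruitment differs by arm and the baseline may be affected

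*Protocol article*

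**What the plan says.** The Study design section randomises clusters: "Neighbourhoods will be randomized per set of two neighbourhoods with comparable household incomes to either the control or intervention condition".

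Study procedures then describes recruitment of individuals. Care staff screen with a checklist for potential eligibility. Of those identified, the article says: "These people will be informed about the study and will be asked to participate by the research team". It adds that "in the intervention group they will be invited to visit an informative meeting about the study and the intervention". No counterpart for the control group is described.

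The text under Fig. 1 continues: "People who express an interest in the study, will be interviewed face-to-face by one of the researchers". Written consent follows for those who qualify and wish to take part, and then: "Subsequently, the baseline assessment will be completed and the intervention will be carried out in the intervention group". According to Assessment and data collection, the baseline interview includes the PAM-13, the primary outcome.

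The Limitations section concedes that selection bias in identifying candidates cannot be excluded. The safeguard it offers is clear criteria, of which it says: "These criteria are the same in both the intervention arm and the control arm". The Strengths section nevertheless presents the cluster-randomised design as a basis for causal conclusions.

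**The concern.** In a cluster trial that recruits individuals, randomising neighbourhoods protects the comparison only if people enter the two arms by the same route. Here one arm has an additional contact whose stated subject is the intervention. Two separate mechanisms follow.

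1. **Who enrols.** A meeting about advance care planning may attract, or put off, people according to how ready they are to discuss and plan care. That trait lies close to the primary outcome and to the secondary outcomes on directives and surrogates. Controls pass through no such filter.
2. **What the baseline measures.** If the meeting itself moves patient activation, the intervention arm's baseline PAM-13 is not a value from before all exposure. The planned contrast is a difference in change from that baseline.

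Identical eligibility criteria settle who may enrol. They do not equalise who volunteers after receiving different information.

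**Working it through.** **Order of events.** The people invited to the meeting are those whom staff have flagged and the research team is asking to take part, so they are not yet enrolled. Interest, interview, consent and baseline come afterwards in the text. The meeting is introduced as an addition to the invitation and carries no date. That it precedes consent and baseline is therefore an inference. Nothing in the text contradicts it, but the flow chart could not be checked.

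**The plan's own figure.** Inputs from Sample size: power 0.80, alpha 0.05 (taken as two-sided), difference 0.5 SD, average cluster size 12, ICC 0.05.
- Unclustered: n = 63 per arm (normal approximation).
- Design effect: 1 + (12 − 1) × 0.05 = 1.55.
- Clustered: 63 × 1.55 = 97.65, rounded up to 98 per arm; power 0.803.

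The figure reproduces and is not in dispute. The implied standard error of the between-arm contrast is √(2 × 1.55 / 98) = 0.178 SD.

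**Selection.** Let the enrolled groups differ by a stable amount d in PAM, and let Δ be the true effect.
- Difference in change: (Δ + d) − d = Δ. A stable difference cancels.
- It does not cancel if those enrolled in one arm respond differently from those enrolled in the other.
- Advance directives, surrogate appointment and use of care have no stated baseline measurement, so there is nothing to subtract and d stays in the contrast.

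**Baseline shift.** Let the meeting raise mean baseline PAM in the intervention arm by b. If a share a attends and attenders move by s, then b = a × s. Let a fraction p of the shift persist to 12 months, and let F be the effect of the facilitator meetings.
- Difference at 12 months: F + p·b. Difference in change: F + p·b − b.
- If the meeting counts as part of the intervention, the target is F + p·b and the result is understated by b.
- If the target is F alone, the result is understated by (1 − p)·b. A shift that fully persists then causes no bias.

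**Illustration with assumed values.** The article gives no size for either mechanism. With standard error 0.178 SD:

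| Assumed bias (SD) | Two-sided type I error if it adds to the contrast | Power at true 0.5 SD if it is subtracted |
|---|---|---|
| 0 | 0.05 | 0.80 |
| 0.05 | 0.059 | 0.72 |
| 0.1 | 0.087 | 0.61 |
| 0.2 | 0.20 | 0.39 |
| 0.3 | 0.39 | 0.20 |

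The middle column applies only to bias that survives the analysis, and so not to a stable PAM difference under change scores. The right-hand column uses the plan's SD for PAM. A change score has that same SD when the baseline-to-12-month correlation is 0.5, since 2(1 − 0.5) = 1. A larger sample removes neither bias.

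**The case against.** The strongest reply is that much of this is inferred. No sentence dates the meeting, and the article reports neither its content, nor attendance, nor any effect on PAM. A reader might infer that the baseline is known to be contaminated; the text supports only that it may be.

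A reader might also take an assumed 0.1 to 0.2 SD difference between volunteers and divide by 0.5 to get a bias of 20 to 40% of the target. That does not fit the Statistical analysis section, which compares changes: a stable difference largely cancels there.

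The baseline shift, where it exists, works against finding an effect. It shrinks if few attend, and drops out if it persists and only the facilitator meetings are the target. These points limit the size. They do not remove the asymmetry.

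The article also has partial safeguards. It compares baseline characteristics by arm and adjusts for patient characteristics, frailty score, MMSE and place of residence. None of these measures willingness to engage in care planning.

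Two further inferences lack support:
- **Staff judgement biased by allocation.** Eligibility includes being "Mentally competent, as measured by judgement of caregiver", and the first screening step reads "Staff of the care organisation will use a checklist to assess whether participants" are potentially eligible. But the caregiver is not said to be the organisation's staff, the MMSE and frailty thresholds apply as well, and whether screeners know the allocation is not stated.
- **Recruitment counts by arm missing.** The article commits to CONSORT and cites a flow chart.

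**Conclusion.** The point holds as a risk of bias. As written, recruitment differs by arm through a meeting about the intervention, and the safeguard in the Limitations section does not reach it. The protection of randomisation is weakened. A reader might go further and say that it is removed, but the documents do not support that: clusters are still randomised in matched pairs, and part of any selection effect on PAM cancels in the change.

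Exposure is greatest for advance directives, surrogate appointment and use of care. For PAM it depends on differential response among those enrolled, or on a baseline shift that belongs to the intervention's effect. Size and direction are not identifiable from the article; the tabulated values are assumptions. The conclusion rests on the natural reading that the meeting precedes consent and baseline. If the full protocol or the flow chart places it after baseline, both mechanisms fall away.

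**What to change.** Hold the intervention-specific meeting after written consent and the baseline interview. Before that point, use the same invitation route and the same study information in both arms. Information needed for consent can be given individually at the face-to-face interview, where the article already plans to give additional information.

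If the order cannot be changed, name the arm-specific meeting under Limitations and soften the causal claim under Strengths.

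The main change is one of sequence. The cost is that uptake in the intervention arm may be somewhat lower. Some arm-specific information may still be needed before consent, so the asymmetry may be reduced rather than fully removed.

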### Intervention

Older people in the intervention group will be offered the Respecting Choices program in addition to their usual care. This program, developed in the US, involves trained nurse facilitators who, in collaboration with physicians, assist residents and their relatives in reflecting on the resident’s goals, values and beliefs and in discussing their health care wishes [11, 16]. This discussion also supports people to identify specific activities and experiences that may contribute to, or detract from, their quality of life. Residents are encouraged to appoint a surrogate decision-maker, and to document their wishes about the care they do or do not want to receive in an advance directive. These wishes can e.g. concern the (non)use of burdensome life-prolonging interventions such as hospitalization or cardio-pulmonary resuscitation. For our study, a nurse practitioner followed the Respecting Choices train-the-facilitators program in the US. She will deliver the training program for the facilitators. These are nursing staff members of Laurens, who will deliver the intervention to the study participants. The intervention concerns two meetings of a facilitator with a participant of 1 h. The content of the communication during these meetings will be structured by the use of interview cards.

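### An information meeting offered to intervention-arm candidates only, apparently before consent and baseline, risks differential recruitment and may shift baseline PAM in one arm

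*Protocol article*

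**What the plan says.** Neighbourhoods are randomised in income-matched pairs (Study design). Under Study procedures, care staff first list potentially eligible people. The next step is common to both arms: "These people will be informed about the study and will be asked to participate by the research team". The following sentence applies to one arm only: "in the intervention group they will be invited to visit an informative meeting about the study and the intervention".

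The text around Fig. 1 then continues the sequence:
- An interview comes first: "People who express an interest in the study, will be interviewed face-to-face by one of the researchers"
- Consent in writing is taken next, from those who qualify and agree.
- Baseline and then the programme come last: "Subsequently, the baseline assessment will be completed and the intervention will be carried out in the intervention group"

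The Intervention section defines the programme separately: "The intervention concerns two meetings of a facilitator with a participant of 1 h". The information meeting is not listed as part of it.

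PAM-13 is the primary outcome and is measured at baseline and at 12 months. The Statistical analysis section plans "to compare differences in changes after 12 months following the inclusion", with patient characteristics, TFI score, MMSE score and place of residence as covariables. On selection bias, the Limitations section says: "To prevent this as much as possible, we have prepared clear in and exclusion criteria", and adds that the criteria are the same in both arms.

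**The concern.** The concern is what happens to listed people between listing and the baseline interview, not whom staff list. That one arm is handled differently at this stage implies that allocation is already known when individuals are approached. Two consequences follow.

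**Differential consent.** Intervention candidates can decide after hearing the programme presented at a meeting, and control candidates are not offered that meeting. Those who consent may then differ between arms in their interest in care planning and medical decision-making, which lies close to the primary outcome. Age, competence, language and frailty criteria do not balance willingness to engage, and none of the named covariables measures it. Randomising neighbourhoods does not protect against this, because the selection happens afterwards.

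**A possibly shifted baseline.** If the meeting itself raises activation among those who attend, the intervention-arm baseline PAM already contains part of the effect. A comparison of changes then subtracts that part. The cost-effectiveness ratio, which divides by the average change in effectiveness, would carry the same error.

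**Working it through.** **1. Order of steps.** Read in sequence, Study procedures gives: listing by staff; approach in both arms; meeting invitation in the intervention arm; expressed interest; interview; consent; baseline; intervention. Those invited are the potentially eligible people, not consented participants, and the meeting's subject includes the study itself. It therefore reads as a recruitment step. This is the natural reading, not a stated date.

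**2. The plan's own figure.** Inputs from Sample size: difference 0.5 SD, alpha 0.05 (two-sided assumed, since sidedness is not stated), power 0.8, cluster size 12, ICC 0.05.
- The two-sided normal approximation gives 63 per arm, as stated.
- Design effect = 1 + (12 − 1) × 0.05 = 1.55.
- 63 × 1.55 = 97.65, rounded up to 98 per arm, as stated.
- SE = √(2 × 1.55 / 98) = 0.178 SD.
- Power = Φ(0.5/0.178 − 1.96) = 0.803.

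**3. Baseline shift, unadjusted change score.** Assumptions: the 12-month difference stays at 0.5 SD, the change score has the same SD as the outcome (a baseline/follow-up correlation of 0.5), and the arm-average baseline shift is a fraction of 0.5 SD. The documents give no value for that fraction.

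| Fraction before baseline | Baseline shift (SD) | Change contrast (SD) | Power |
|---|---|---|---|
| 0% | 0 | 0.500 | 0.80 |
| 5% | 0.025 | 0.475 | 0.76 |
| 10% | 0.050 | 0.450 | 0.72 |
| 20% | 0.100 | 0.400 | 0.61 |

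The shift is an average over the whole arm. For example, 50% attendance with a 0.2 SD shift among attendees gives 0.5 × 0.2 = 0.10 SD, the last row.

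**4. Same shift, baseline PAM as covariate.** With an assumed slope of 0.5, half the bias remains. At 10% and 20% the contrasts are 0.5 − 0.025 = 0.475 and 0.5 − 0.05 = 0.45 SD. If the SE is left at 0.178, power is 0.76 and 0.72. If the gain in precision is also counted (residual variance 1 − 0.5² = 0.75, same design effect), SE = 0.178 × √0.75 = 0.154 and power is about 0.87 and 0.83.

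**5. Same shift, 12-month PAM only.** The baseline value is not used, so the contrast stays at 0.5 SD and power at 0.80.

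**6. Differential consent.** Its size cannot be derived from the documents. As an illustration, suppose self-selection shifts intervention-arm baseline PAM by 0.2 SD.
- If that difference regresses with correlation 0.5, the raw change contrast is biased by (1 − 0.5) × 0.2 = 0.10 SD, in a direction that depends on who opts in. Adjusting for baseline PAM removes this bias under the same model.
- If the difference is stable, the change score carries no such bias, but a comparison of 12-month PAM alone carries all of it.

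No single analysis deals with both effects together.

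**The case against.** Several points on the other side have force.

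- **Timing.** No sentence dates the meeting relative to consent or baseline, and the flow chart that might settle it is not shown. This stands: the order is inferred.
- **Exposure.** A reader might infer that the intervention-arm baseline PAM is taken after first exposure to the intervention. The documents do not support that. They define the intervention as two facilitator meetings and place it after baseline. The information meeting is by invitation and its content is not described. Nothing shows that it moves a scale of knowledge, skill and confidence in self-management. What can be said is that baseline PAM may be shifted.
- **Control information.** Both arms are informed by the research team and again in the pre-consent interview, and nothing says that controls are not told about advance care planning. This also stands, so the two arms may consent on different information. What is certain is that one arm is offered an extra meeting.
- **Repair in analysis.** A reader might infer that neither effect can be repaired. For each taken alone that is wrong, as steps 5 and 6 show. The article does not say whether baseline PAM is a covariable, so pure subtraction is the unfavourable case. Unmeasured motivation, however, would not be removed by the covariables named.
- **Direction.** A baseline raised by the meeting pulls toward no effect and cannot itself create a false positive. Selection through consent has no fixed direction.

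The Limitations section does concede that selection bias is possible. It does so for the identification of potential participants and answers with equal criteria. It does not address an extra recruitment step in one arm.

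**Conclusion.** The point holds as a risk built into a stated, arm-specific recruitment step. The firmer part is differential recruitment: once allocation is known, one arm is offered additional information, apparently before consent, and identical criteria do not balance who agrees. Its size cannot be computed from the documents.

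The second part is conditional. If the meeting precedes baseline and raises PAM by 5% to 20% of 0.5 SD averaged over the arm, an unadjusted change-score analysis loses power from 0.80 to between 0.76 and 0.61. The loss is smaller with baseline adjustment, and there is none if PAM does not move. The shift, the slope and the correlation are all assumptions. The planned sample size is reproduced and is not in dispute.

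**What to change.** - State when the meeting takes place relative to consent and baseline.
- Hold the intervention-specific meeting after written consent and the completed baseline assessment.
- Before consent, use the same neutral study information in both arms. If a recruitment meeting is needed, hold the same neutral one in both.
- For people already recruited, record and report by arm the numbers approached, attending and consenting.
- Add a sensitivity comparison of 12-month PAM that does not use the baseline value. This addresses the baseline shift only, not differential consent.
- Do not exclude meeting attendees. Controls have no equivalent group, so this would remove self-selected people from one arm, depart from intention to treat, and add selection bias.

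The cost is a reordering of existing steps and one common information text. Intervention-arm recruitment may be slightly slower, or a few neutral meetings may be needed in control neighbourhoods.
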